### Data and biosample collection

Study data will be collected by trained research staff using an access-controlled, web-based database (MedSciNet, Stockholm) managed with support from the data management staff of the MRC Lifecourse Epidemiology Unit and the Singapore Institute for Clinical Sciences. The study database will not hold personal information, which will be stored separately at each institution with access limited to study coordinators. Data from the web-based database will be downloaded via a dedicated computer and stored securely on the MRC Lifecourse Epidemiology Unit’s servers in the UK. Data extracts will be provided for analysis by the study researchers treating data from all three sites as a single study. All data will be kept in accordance with the UK Data Protection Act, and applicable regulations and guidance of each country and institution.

Biological samples will be collected and processed using standardised consumables, equipment and protocols across the three sites and will be being stored in accordance with the UK Human Tissue Act or equivalent at each institution in appropriately regulated biobanks. The study database allows management of the samples. All analysis will be carried out on anonymised data and samples. Accredited laboratories will be used for measurement of the primary outcome of plasma glucose concentrations.

### Study management and governance

This double-blind randomised controlled trial is led by investigators from the EpiGen Global Research Consortium, an academic research consortium comprising representatives from the University of Southampton (MRC Lifecourse Epidemiology Unit and Institute of Developmental Sciences), University of Auckland (Liggins Institute), the Growth, Development, and Metabolism Programme of the Singapore Institute for Clinical Sciences (an operating unit of A*STAR) and the National University of Singapore (Translational and Clinical Research Flagship Programme, ‘Developmental pathways to metabolic disease’), together with the Singapore National University Health System. Scientists from the Nestlé Research Centre (Nestec) provided advice on aspects of the intervention formulation, study design and specific laboratory analyses.

The UK sponsor of the project is the University of Southampton; the New Zealand sponsor of the project is Auckland UniServices Limited; the Singapore sponsor of the project is the National University Hospital Singapore. The sponsors are indemnified for any harms arising from trial participation and will approve protocol amendments for which ethics approval has been secured, alongside update of trial registry entries. Trial oversight will be provided by an Independent Data Monitoring and Safety Committee. The day-to-day running of the study will be through the Trial Management Group, consisting of the principal investigators and the clinical trial operations director, who will be responsible for all decisions on the study management and delivery.

Monitoring will be carried out several times per year by an external, independent monitor at each site, following the risk-based monitoring plan established for the study, overseen by the study sponsor. Safety reporting will be in accordance with the study Safety Monitoring Plan and all events will be recorded in the study database. An Independent Data Monitoring and Safety Committee has been established for the trial. This committee is independent from the sponsor and competing interests and will meet annually and oversee all ethical and safety issues in accordance with current regulations and MRC guidelines for Data Monitoring Committees. The Committee Charter is available from the clinical trial operations director, who will coordinate and review activity across sites.

### Statistical analysis

The primary analysis will be according to the intention-to-treat principle. Additionally, a priori sensitivity analyses will be undertaken, omitting participants withdrawn as a consequence of reluctance to continue with the trial, conception after taking the nutritional drink for less than 21 days, less than 60% uptake with the intervention (evidenced by sachet counting), not conceiving after 12 months of participation or not achieving a pregnancy of more than 28 weeks. Further sensitivity analyses using a ‘per protocol’ or an ‘as treated’ analysis will be performed if deemed appropriate by the trial statisticians. For analysis of the primary endpoint only: if exploratory analysis reveals the presence of outliers, as identified by independent experts and/or the trial statisticians, sensitivity analysis will be performed excluding these outliers. Analyses will be specified in the study statistical analysis plan finalised by the Trial Management Group before unblinding the data. The influence of missing data will be examined using multiple imputation techniques. There are no formal planned interim analyses of the primary outcome, but progress reports on all data issues will be presented to the Independent Data Monitoring and Safety Committee, who will agree their charter at their first meeting. Analyses of the baseline phenotypic data that do not require unblinding will be undertaken. We will build prognostic models using baseline covariates on the primary outcome of maternal glucose tolerance in pregnancy. Planned subgroup analyses will include stratification by ethnicity across study sites.

### Power calculations

By studying up to 900 prepregnant participants in each of the intervention and control groups, a total of 600 pregnancies and 500 live births is conservatively anticipated, following attrition from miscarriage, ectopic pregnancy, perinatal demise, multiple pregnancy, voluntary participant withdrawal, inability to comply with the protocol, withdrawal for medical reasons at the discretion of the investigator and loss-to-follow-up. A study of 250 pregnancies with 28-week OGTT data in each group has 89% power to detect a 0.1-mmol/L reduction in fasting plasma glucose and 84% power to detect a 0.3-mmol/L reduction in 2-h plasma glucose at the 5% level of significance. In the Hyperglycemia and Adverse Pregnancy Outcomes (HAPO) study such changes in glucose concentrations were associated with >10% changes in the odds of macrosomia and sum of neonatal skinfolds >90th centile and with a >20% change in cord C-peptide >90th centile [6]. As a further illustration of statistical power, using the distribution of 60-min plasma glucose in the HAPO study, a study of 250 participants in each of the two groups has 80% power to detect a difference of ≥0.43 mmol/L in 60-min glucose at *P* < 0.05. A study of 300 pregnancies in each arm will have an 80% power to detect a reduction in the mean plasma glucose of 0.12, 0.45 and 0.34 mmol/L at fasting, 60 min and 2 h, respectively, with an alpha of 0.017 taking into account multiple testing.

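### The 89% and 84% power stated for fasting and 2-h glucose at 250 per group do not fit the detectable differences stated for 300 per arm

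*Protocol article*

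**What the plan says.** All the figures are in the Power calculations section of the protocol article, in three statements.

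1. With 28-week glucose data from 250 women per arm, the trial "has 89% power to detect a 0.1-mmol/L reduction in fasting plasma glucose and 84% power to detect a 0.3-mmol/L reduction in 2-h plasma glucose"; alpha is 5%. The section then ties differences of this size to neonatal outcomes in the HAPO study.
2. As an illustration, "using the distribution of 60-min plasma glucose in the HAPO study", 250 per group is given "80% power to detect a difference of ≥0.43 mmol/L in 60-min glucose" at P < 0.05.
3. With 300 per arm, 80% power and an alpha of 0.017 for multiple testing, the trial is said to detect a "reduction in the mean plasma glucose of 0.12, 0.45 and 0.34 mmol/L at fasting", 60 min and 2 h respectively.

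No SD or sidedness is given for any of these, and none is linked to covariate adjustment. The Outcome measurements section says that the primary analysis adjusts for site, ethnicity and preconception glycaemia.

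**The concern.** For a fixed SD, sample size, alpha, power and detectable difference determine one another. Statements 1 and 3 concern the same fasting and 2-h measurements, so they should lead back to the same SDs. They do not.

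These are the power figures for the primary endpoint, quoted at the differences the section presents as meaningful. If the SDs behind statement 3 are right, the chance of missing a true 0.1 mmol/L fasting effect at 250 per group is about 31%, not 11%. A null fasting or 2-h result would then be read as stronger evidence of no effect than the design can give.

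**Working it through.** **Inputs** (all from Power calculations): 250 per group, alpha 0.05, with 0.1 mmol/L at 89% (fasting), 0.3 at 84% (2-h) and 0.43 at 80% (60-min); 300 per arm, alpha 0.017, 80% power, with 0.12, 0.45 and 0.34 (fasting, 60-min, 2-h). Two-sided tests are assumed first.

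**Formula** (two equal groups, normal approximation): difference = SD × (z for alpha + z for power) × √(2/n). Hence SD = difference / [(z for alpha + z for power) × √(2/n)].

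**Implied SDs (mmol/L).** √(2/250) = 0.0894 and √(2/300) = 0.0816.

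| Time point | 250 per group, 5% | 300 per arm, 0.017 |
|---|---|---|
| Fasting | 0.1 / [(1.960 + 1.227) × 0.0894] = 0.351 | 0.12 / [(2.387 + 0.842) × 0.0816] = 0.455 |
| 60-min | 0.43 / [(1.960 + 0.842) × 0.0894] = 1.716 | 0.45 / [(2.387 + 0.842) × 0.0816] = 1.707 |
| 2-h | 0.3 / [(1.960 + 0.994) × 0.0894] = 1.135 | 0.34 / [(2.387 + 0.842) × 0.0816] = 1.290 |

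The 60-min pair is reproduced: an SD of 1.707 gives 80.4% power for 0.43 mmol/L at 250 per group. So the formula and a two-sided convention fit statements 2 and 3. The fasting SDs differ by 30% and the 2-h SDs by 14%.

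**The same conflict without choosing an SD.** The multiplier of the SD is 0.285 for 250 per group, 5% and 89%, but 0.264 for 300 per arm, 0.017 and 80%. With one fasting SD, the second design should detect a smaller difference than the first: 0.092 rather than 0.1 mmol/L. The article prints a larger one, 0.12. For 2-h both multipliers are 0.264, so 0.3 should stay at 0.30; the article prints 0.34.

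**Power at 250 per group with the SDs from statement 3**, two-sided 5%:
- Fasting: Φ(0.1 / (0.455 × 0.0894) − 1.960) = 69%, against 89% stated.
- 2-h: Φ(0.3 / (1.290 × 0.0894) − 1.960) = 74%, against 84% stated.
- Replacing 1.960 by 2.387 (alpha 0.017) gives 53% and 58%.

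**Alternatives tried**
- *Rounding of 0.12 and 0.34 by ±0.005:* fasting SD 0.436–0.474 (power 65–73%), 2-h SD 1.271–1.309 (73–75%). Rounding of 89% by half a point gives a fasting SD of 0.348–0.354. The ranges do not meet.
- *t instead of normal distribution:* 0.350 against 0.454, and 1.133 against 1.287.
- *One-sided throughout:* 0.389 against 0.496, and 1.271 against 1.406. The 60-min pair then stops agreeing (1.933 against 1.861).
- *One-sided 5% in statement 1 only:* 2-h power becomes 83% (82–84% with rounding), which fits. Fasting becomes 79% (76–82%), which does not.
- *300 per arm in statement 1:* fasting power is 77%, at most 80%.

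**The case against.** The article never says that both statements use one SD, and HAPO is named as a source of the distribution only for the 60-min illustration. The primary analysis adjusts for preconception glycaemia, so statement 1 might rest on a smaller, residual SD. The correlation with baseline that this needs is √(1 − (0.351/0.455)²) ≈ 0.64 for fasting and √(1 − (1.135/1.290)²) ≈ 0.47 for 2-h. These are assumed values; the document gives none. The explanation is possible, but the power text does not mention it, and if it is true the paragraph mixes adjusted and unadjusted figures without saying so.

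Another possibility is that 0.1 and 0.3 are themselves rounded to one decimal. With the larger SDs, 89% and 84% power at 250 per group correspond to 0.455 × 0.285 = 0.130 and 1.290 × 0.264 = 0.341 mmol/L, which round to 0.1 and 0.3. That would reconcile the SDs, but it would also mean that the stated power does not apply to the differences as printed.

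The 60-min figure stands in a separate sentence, so its agreement shows a two-sided convention for statements 2 and 3 and only suggests it for statement 1. This makes the 2-h conflict weaker than the fasting one.

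Finally, the section starts from recruitment and attrition and then reports the power that follows, so 250 per group was not visibly derived from 89% and 84%. That is fair, and it limits the consequence: no sample size or analysis changes. The stated power still has to be right.

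**Conclusion.** The point holds. At the printed differences, with a comparison of two means and two-sided tests, statements 1 and 3 imply different SDs for fasting and 2-h glucose, so the 89% and 84% cannot stand beside 0.12 and 0.34 mmol/L for one SD per time point. Fasting is the firm part: no variant of sidedness, rounding of 0.12 and of the power, or choice of distribution closes the gap. The 2-h part depends on statement 1 being two-sided.

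If the larger SDs are right, power at 250 per group and 5% is about 69% (65–73%) for fasting and 74% (73–75%) for 2-h. If the smaller SDs are right, 300 per arm at alpha 0.017 detects about 0.092 and 0.30 mmol/L, and statement 3 is the one that is wrong. The document cannot decide between these. The 60-min figures are consistent and need no correction on this account.

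**What to change.** Set one SD for each of fasting, 60-min and 2-h glucose. Give its source and say whether it is raw or residual after baseline adjustment. Recompute every power figure from that set, with two-sided tests, at 250 per arm and at the alpha that the primary test will use, and give the differences to two decimals.

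If the larger SDs are correct, replace 89% and 84% with about 69% and 74% (at 5%) or 53% and 58% (at 0.017). If the smaller ones are correct, keep 89% and 84% for the 5% level and change 0.12 and 0.34 to about 0.09 and 0.30. If statement 1 was one-sided or baseline-adjusted, say so and put the other statements on the same basis.

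The cost is a recalculation and a rewritten paragraph. The stated power may become less favourable. No participants are added and no analysis changes.

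### The only multiplicity-adjusted power figure counts every anticipated pregnancy (300 per arm); at 250 per arm with an OGTT it is about 71% on that sentence's own SDs, and the section's two sets of figures imply different SDs

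*Protocol article*

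**What the plan says.** All the figures stand in one paragraph of the protocol article, under Power calculations.

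- Yield: "a total of 600 pregnancies and 500 live births is conservatively anticipated", after a list of causes of attrition.
- Power at the 5% level: the sample size is described as "A study of 250 pregnancies with 28-week OGTT data in each group". For fasting glucose the article gives 89% for a difference of 0.1 mmol/L. For 2 h it claims "84% power to detect a 0.3-mmol/L reduction in 2-h plasma glucose at the 5% level of significance". At the same size, the 60-min comparison "has 80% power to detect a difference of ≥0.43 mmol/L in 60-min glucose".
- Power with multiplicity adjustment: "A study of 300 pregnancies in each arm will have an 80% power to detect a reduction in the mean plasma glucose". The differences are listed as "0.12, 0.45 and 0.34 mmol/L at fasting, 60 min and 2 h, respectively". The significance level is given by the phrase "with an alpha of 0.017 taking into account multiple testing".

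Elsewhere, Outcome measurements defines the primary endpoint as any or all of fasting, 60-min and 2-h glucose. It restricts the primary analysis to pregnancies reaching 28 weeks and adjusts for site, ethnicity and preconception glycaemia. The withdrawal criteria, under Recruitment, remove women for miscarriage, ectopic pregnancy, multiple pregnancy and low uptake of the drink, among other reasons.

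**The concern.** With three glucose measures in the primary endpoint, the alpha-0.017 sentence is the one that matches the design. It is also the only sentence whose n is a count of pregnancies rather than of women with the outcome measured. Three hundred per arm is 600 / 2, so it allows no loss between a recognised pregnancy and the 28-week OGTT. The plan's own withdrawal rules make some loss certain. The section therefore has no power figure with both the adjusted alpha and a realistic number of OGTTs, and a reader will take 80% as the trial's power when it is likely to be lower.

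A second problem appears when the figures are compared. The section states no SDs, and those implied by the two sets of statements do not agree for two of the three measures.

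**Working it through.** **Method.** Two-sided comparison of two means, equal arms, normal approximation (sidedness is not stated, so two-sided is assumed):

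power = Φ(δ / (σ√(2/n)) − z₁₋α/₂), and so σ = δ / ((z₁₋α/₂ + z_power)·√(2/n)).

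Constants: z = 1.960 for alpha 0.05 and 2.387 for alpha 0.017; z = 0.842, 0.994 and 1.227 for power 80%, 84% and 89%; √(2/250) = 0.0894; √(2/300) = 0.0816.

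**Step 1: SDs implied by each set.**

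| Measure | 250 per arm, alpha 0.05 | 300 per arm, alpha 0.017, 80% |
|---|---|---|
| Fasting | 0.1 / (3.187 × 0.0894) = 0.351 | 0.12 / (3.229 × 0.0816) = 0.455 |
| 60 min | 0.43 / (2.802 × 0.0894) = 1.716 | 0.45 / (3.229 × 0.0816) = 1.707 |
| 2 h | 0.3 / (2.954 × 0.0894) = 1.135 | 0.34 / (3.229 × 0.0816) = 1.290 |

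**Step 2: reproduce the stated 80%.** With the SDs from the 5%-level set, power at 300 per arm and alpha 0.017 is 96.4% (fasting, 0.12), 79.5% (60 min, 0.45) and 90.0% (2 h, 0.34). Only the 60-min figure reproduces 80%. A t-test gives 96.3%, 79.3% and 89.8%. Reading alpha as one-sided throughout does not reconcile the sets either (fasting SD 0.389 against 0.496).

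The other direction shows the same conflict. With the SDs from the alpha-0.017 set, the stated 89%, 80% and 84% become 69%, 80% and 74%. Fasting and 2 h agree only if 0.1 and 0.3 are one-decimal roundings of about 0.455 × 3.187 × 0.0894 = 0.13 and 1.290 × 2.954 × 0.0894 = 0.34.

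**Step 3: move the alpha-0.017 sentence to 250 per arm.** If 80% at 300 is right, the noncentrality is 2.387 + 0.842 = 3.229. At 250 it is 3.229 × √(250/300) = 2.947, and power = Φ(2.947 − 2.387) = Φ(0.560) = 71.2%, the same for all three measures. At 260, 270, 280 and 290 per arm the results are about 73%, 75%, 77% and 78%.

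The differences detectable with 80% power grow by √(300/250) = 1.095: 0.12 → 0.131, 0.45 → 0.493, 0.34 → 0.372 mmol/L.

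**Step 4: the same step with the SDs from the 5%-level set.** Power at 250 per arm and alpha 0.017, for 0.12, 0.45 and 0.34, is 92.5%, 70.7% and 83.2%. The differences detectable with 80% power are 0.101, 0.495 and 0.328 mmol/L. The two routes agree for 60 min (70.7% and 71.2%) and part for fasting and 2 h.

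**Step 5: a check that needs no SD.** Keep the differences quoted at 250 per arm (0.1, 0.43 and 0.3) and change only alpha from 0.05 to 0.017. Power becomes Φ(3.187 − 2.387) = 79%, Φ(2.802 − 2.387) = 66% and Φ(2.954 − 2.387) = 71%, against the stated 89%, 80% and 84%.

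**The case against.** A reader might infer that the stated 80% is simply wrong and is really 71%. The document does not support that, for four reasons.

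- The sentence is conditional on 300 per arm. Moving to 250 changes its premise; it does not show a miscalculation on that premise.
- The article nowhere says that 250 per arm is the expected number of OGTTs. The 250 appears as a scenario, and the 500 are live births. Perinatal deaths and late withdrawals can fall after the 28-week test, so more than 250 per arm might have an OGTT. The attrition list may also govern the 600, which would then already be net of some losses, and the yield is described as conservative.
- The 71% rests on the SDs behind the alpha-0.017 sentence. On the SDs behind the 5%-level figures, fasting and 2 h would have about 92% and 83% at 250 per arm.
- All these figures are for unadjusted means. The planned adjustment for preconception glycaemia would restore 80% at 250 per arm if 1 − r² = 250/300, that is, r of about 0.41. The article gives no correlation, so this is an assumption.

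These points stand as limits on the size of the shortfall. They do not remove the mismatch. Reaching 300 per arm requires that none of the 600 anticipated pregnancies misses the OGTT, and the power section claims no gain from covariates. The SD conflict is also a reason to correct the paragraph.

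**Conclusion.** The concern holds in a limited form. The one multiplicity-adjusted power statement rests on all 300 anticipated pregnancies per arm, while the rest of the paragraph counts women with a 28-week OGTT and the primary analysis needs pregnancies that reach 28 weeks.

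On the SDs behind that statement, the realistic range is about 71% to 80% for 250 to 300 women per arm. The lower end is firm for 60 min, where both sets of figures agree. It is conditional for fasting and 2 h, where the article contradicts itself on the SD unless two of its differences are coarsely rounded. The assumptions are a two-sided test, equal arms, no covariate gain, and 250 per arm as the lower bound for OGTTs.

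It would go too far to conclude that the trial is underpowered for its primary endpoint. The change in detectable difference is about 0.01 to 0.03 mmol/L for fasting and 2 h and 0.04 mmol/L for 60 min, and the article does not present 0.12, 0.45 and 0.34 as minimum important differences.

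**What to change.** 1. Define n throughout the section as women with a 28-week OGTT, and state how many per arm are expected after attrition.
2. State the SD used for each of the three measures, and give 0.1 and 0.3 to the same precision as the other differences.
3. Reconcile the two sets of figures before rescaling either. Rescaling the alpha-0.017 sentence alone would leave the conflict in place. If the larger SDs are right, the 89% and 84% must also change, to about 69% and 74% for exactly 0.1 and 0.3 mmol/L.
4. Restate the alpha-0.017 sentence at the expected OGTT number. If that is 250 per arm and the larger SDs hold, give about 71% power for 0.12, 0.45 and 0.34 mmol/L, or 80% power for about 0.13, 0.49 and 0.37. If the SDs behind the 5%-level figures hold, the 80%-power differences are about 0.10, 0.50 and 0.33.
5. If a gain from adjusting for preconception glycaemia is to be claimed, state the assumed correlation.

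The cost is a few sentences and possibly a less favourable figure. Recruitment, endpoint and analysis do not change.

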## Discussion

This double-blind randomised controlled trial in groups of women from different ethnic groups in the UK, Singapore and New Zealand is designed to examine the hypothesis that a nutritional drink, commencing before conception and continuing during pregnancy, will assist in the maintenance of healthy glucose metabolism in the mother and promote offspring health. Improved maternal nutrition and glycaemic control before and during pregnancy has benefits for the health of the mother and her offspring, including healthy offspring body composition and decreased risks of childhood obesity and allergies. The intervention group will receive a nutritional drink enriched with micronutrients, myo-inositol and probiotics, and the control group will receive a drink enriched with standard micronutrients. The potential for adverse effects of the intervention is low as the probiotic and myo-inositol are thought to exert their main effects through physiological modulation of maternal metabolism rather than through direct effects on the fetus and, while the amounts of micronutrients in the nutritional drink are sufficient to rectify maternal deficiency, they do not exceed UK, Singapore and New Zealand safe upper limits.

The trial commences preconception as studies by Catalano et al. [53] suggest that a major part of the risk of macrosomia originates in early pregnancy/prepregnancy and adverse pregnancy outcomes are associated with poor maternal nutrition at conception; maternal insulin resistance and hyperglycaemia in the very earliest stages of pregnancy alter placental anatomy and physiology in ways that persistently affect transplacental fetal nutrient supply and fetal fat accretion, as well as bilateral maternal-feto-placental cross-talk, with consequences for later postnatal health. As a consequence, intervention commencing in established pregnancy can only partially influence fetal growth and development. The earlier that maternal glycaemia is optimised and micronutrient deficiencies prevented, the greater the likelihood of maintaining fetal and postnatal health and wellbeing. Many influential governmental and nongovernmental organisations are now stressing the importance of optimising preconception nutrition in general terms but as yet, other than folic acid to prevent neural tube defects, there are few preconception interventions that are recognised as promoting health benefits for the mother or offspring, and none, apart from folic acid, has a robust evidence base.

In the initial phase of the NiPPeR study a broad range of maternal nutritional assessments, potential epigenetic mechanisms and secondary measures relating to pregnancy outcomes and infant growth, body composition and wellbeing will be characterised and are detailed in this protocol.

The extensive biosampling and detailed phenotyping embedded in the study before, during and after pregnancy will provide an important discovery pipeline for the development of novel biomarkers of maternal and offspring wellbeing, and lead to new interventions and future guidelines to promote healthy human growth and development. A range of biological samples collected at multiple time points before, during and after pregnancy in the mother and offspring enables a systems biology approach to understanding the complex interaction of factors that determine maternal and infant wellbeing. Both individually and collectively, the control and intervention arms will provide extensive information that will deliver new knowledge on how maternal nutrition and metabolic state can promote offspring health. The research will also benefit from insights arising from other studies by the EpiGen Global Research Consortium in the UK, Singapore and New Zealand. The ethnicities of the participants in the study will allow broad extrapolation of the findings, and enable subsequent smaller-scale studies in other jurisdictions, such as China and India, as appropriate. The partners have extensive experience of following up prospective mother-offspring cohorts, maternal, obstetrical, fetal and infant medicine and health care, and detailed characterisation of a comprehensive set of health and wellbeing outcomes through infancy and childhood will be undertaken. The data collected will allow determination of the contributions of nutritional and lifestyle factors, socioeconomic status, ethnicity, genetics, transcriptomics, epigenomics, metabolomics and metagenomics to maintaining healthy glucose metabolism in pregnancy and promoting healthy growth, body composition and wellbeing in the offspring.

